### Risk stratification and treatment planning tools

2.8

The leading rules used in designing the treatment plan are these described in European Society of Cardiology respective guidelines.^[11,21,22]^ For precise risk stratification we use the following scores:

Syntax score I and II—www.syntaxscore.com^[5]^;Logistic Euroscore 2—www.euroscore.org^[6]^;GRACE 2.0 score—www.gracescore.org^[23]^;CRUSADE bleeding risk score—www.crusadebleedingscore.org.^[24]^

The final results of each score will be compared between frail, pre-frail, and non-frail patients and will be used for modeling of the outcomes hazard ratio in the follow-up.

### Echocardiographic assessment of left ventricle geometry and function

2.9

We assess left ventricle diameters, volumes, systolic and diastolic function according to American Society of Echocardiography guidelines for chamber quantification.^[25]^ We use Vivid 7 Dimension echocardiographic machine with integrated software (GE, Horten, Norway) for measurements.

### Statistical analysis

2.10

First, we use descriptive and comparative statistical methods to describe the incidence of frailty among symptomatic patients with coronary artery disease and provide extensive characteristics of frail elderly coronary heart disease population. Two-way analyses with *P* < .05 are considered significant. Second, Kaplan–Meier analysis of survival and Cox's proportional hazard analysis will be used for the identification of variables predisposing for outcomes occurrence. Selection of appropriate variables will be based on results of comparative and descriptive statistical analysis. Variables of significance <0.1 will be entered into uni- and multivariate Cox modeling.

According to the data reported by Central Statistical Office of Poland (www.stat.gov.pl), in 2013 the number of deaths from cardiovascular diseases ranged from 2226 to 3086 per 100,000 inhabitants over 65 years of age. These data allow to predict the occurrence of approximately 100 deaths in the study population during 36 months of prospective observation. Power of study based on the mortality data is presented in Fig. 2. The other endpoint is the incidence of new-onset heart failure. In our observations (unpublished data), the incidence of symptomatic heart failure in STEMI-treated patients after myocardial infarction was 16.3% in 12 months. Considering that patients with STEMI infarction will be around 100, we assume at least 45 new episodes of cardiac failure over a 36-month period. These assumptions were necessary for reliable Cox proportional hazard modeling—10 complete observations are required for a reliable estimation of 1 variable. The ancillary analyses will be performed for different subgroups depending on demographic or clinical presentations and we will analyze either crude or adjusted data.^[26]^ All analyses will be performed in Statistica 12.5 (Tulsa, Oklahoma, OK) licensed to Medical University of Silesia.

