## Introduction

1

Frailty gains growing attention of clinical research community as society of developed countries and their cardiovascular patients are aging. Frailty syndrome is characterized by reduced physiological reserve and increased susceptibility to various stressors.^[1]^ Several diseases, either acute or chronic, or iatrogenic circumstances may act as stressors. Frail patients, after being exposed to such stressors, may react with incommensurate decompensation, and adverse outcomes. They are at higher risk of procedural complications, long-lasting recovery, functional deterioration, physical disablement, and increased risk of death.^[2]^ The syndrome is frequently associated with comorbidities.^[3]^ Symptomatic coronary heart disease, either stable or unstable, is the prevailing disease unit among elderly patients. Inversely, data on prevalence of phenotype frailty among patients aged ≥65, who underwent percutaneous coronary angioplasty were recently published.^[4]^ Gharacholou et al^[4]^ reported that approximately 20% of those patients is frail. Moreover, frail patients have greater comorbid burden and greater angiographic coronary artery disease intensity. However, commonly used risk stratification scales, like Syntax,^[5]^ Euro,^[6,7]^ or GRACE^[8]^ use patient's age as a major determinant of risk, but they do not incorporate the frailty traits into the risk assessment. Technical development has allowed more patients to become eligible for interventional treatment.^[9,10]^ As medical innovations are cost consuming, the individual benefits of such medical procedures are not well defined in particular patient populations. Thus, we need to operationalize more detailed patient selection.

The objectives of the study are to report Fried frailty scale and instrumental activities of daily living (IADL) scale dispersion before hospital discharge and to assess the predictive impact of both scores in a population of elderly patients with symptomatic coronary artery disease.

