### Patient population

2.1

The FRAPICA trial is a single center, observational, prospective, study. One thousand patients aged ≥65 years with symptomatic coronary heart disease will be enrolled. Patients with all clinical presentations of coronary artery disease are eligible. Stable coronary heart disease is diagnosed on the base of exercise induced ischemia, resolving after rest. Acute coronary syndrome includes ST segment elevation myocardial infarction, non-ST segment elevation myocardial infarction and clinical presentation of unstable angina. The latter is characterized by myocardial ischemic pain at rest or at minimal physical activity in the absence of myocardial necrosis. Non-ST segment elevation myocardial infarction is diagnosed in patients with symptoms of ischemia, electrocardiographic abnormalities such as ST-segment depression, inversion of T wave, flattened T wave, pseudo-normalization of previously negative T waves, and presence of cardiomyocyte necrosis. ST-segment elevation myocardial infarction is diagnosed when acute precordial pain (>20 minutes), persistent ST-segment elevation, cardiomyocyte necrosis, and typical angiographic findings are present.^[11]^ Either femoral or radial approaches are acceptable—the choice of puncture site depends on patient's or operator's preference and basically on medical conditions. Only patients with type 1 myocardial infarction are considered eligible for the study. Method of revascularization is decided by the operator and ad hoc percutaneous coronary intervention is sometimes performed. Mostly, this is a case in a low-risk patients with single vessel disease, or in cases of ST-elevation myocardial infarction (STEMI) or non ST-elevation myocardial infarction (NSTEMI) patients with identifiable culprit artery. Nevertheless, all coronary angiographies are assessed and discussed by a heart team, selected records are re-consulted with a cardiac surgeon and a further revascularization schedule is planned. For the risk stratification we use Syntax score and logistic Euro score. After performed coronary angiography and confirmation of coronary heart disease with documented significant stenosis, patients are screened and written informed consent is obtained. Protocol of the study was approved by Internal Review Board of Medical University of Silesia. For the purpose of this study we record demographic, clinical, laboratory, angiographic data from patient's medical charts, assess the presence of frailty syndrome, measure arterial stiffness, body composition, pulmonary function, and draw fasting blood for further analyses. Study flowchart is shown in Fig. 1.

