Bleeding is defined after Smith et al^[20]^ as “blood loss at the site of arterial or venous access or due to perforation of a traversed artery or vein requiring transfusion and/or prolonging the hospital stay, and/or causing a drop in hemoglobin >3.0 g/dL. Bleeding attributable to the vascular site could be retroperitoneal, a local hematoma >10 cm diameter or external.” Bleeding from non-access sites like intracranial hemorrhage, gastrointestinal, or genitourinary blood loss will be recorded either to ascertain safety of antiplatelet or anticoagulation treatment in frail patients.

For the assessment of overall patients’ health we will monitor 3-year mortality, either all-cause and cardiovascular, re-infarction, re-intervention, stroke, new-onset heart failure, any hospital readmission, and a combination of all above mentioned. The 36-months long follow-up is based on semi-annual telephone contact with patient or designated family member.

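### Kaplan–Meier is the only named curve or risk estimator for follow-up outcomes; for non-fatal ones it overstates absolute risk when deaths are censored, and more so in frail patients

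*Protocol article*

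**What the plan says.** Section 2.10 (Statistical analysis) names two time-to-event methods: "Kaplan–Meier analysis of survival and Cox's proportional hazard analysis will be used for the identification of variables predisposing for outcomes occurrence". Section 2.7 (Study outcomes) lists what is followed for 36 months: "3-year mortality, either all-cause and cardiovascular, re-infarction, re-intervention, stroke, new-onset heart failure, any hospital readmission", together with a combination of all of these. Section 2.10 also ties its Cox event count to new-onset heart failure, so the time-to-event methods are not reserved for death.

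The Introduction says of frail patients: "They are at higher risk of procedural complications, long-lasting recovery, functional deterioration, physical disablement, and increased risk of death". The Abstract and Conclusion promise a more individual assessment of risk, section 3 (Expected results and possible pitfalls) hopes to separate low-, medium- and high-risk groups, and the Discussion speaks of a risk stratification model to support decisions.

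**The concern.** A patient who dies can no longer have a first stroke, a readmission or new heart failure. Kaplan–Meier with deaths censored treats that patient as if the event could still occur later. It therefore estimates risk in a hypothetical population in which nobody dies first. That figure is higher than the proportion who will actually have the event, and the gap widens with mortality.

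Here the gap would differ between the groups being compared, because frailty is the exposure and frail patients are expected to die more often. Curves by frailty group for a non-fatal outcome would be nearly right in non-frail patients and too high in frail ones. If risk groups or individual risks were read from such curves, the error would pass into the prognostic product of the study.

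**Working it through.** **Inputs from the protocol article**
- Sample size: "One thousand patients aged ≥65 years with symptomatic coronary heart disease will be enrolled" (2.1).
- Follow-up: "The 36-months long follow-up is based on semi-annual telephone contact with patient or designated family member" (2.7).
- Frail share: "approximately 20% of those patients is frail" (Introduction, from a cited cohort treated by percutaneous angioplasty; its use here is an assumption).
- Deaths: "approximately 100 deaths in the study population during 36 months of prospective observation" (2.10).
- Heart failure: 16.3% in 12 months, in STEMI patients, of whom about 100 are expected (2.10).

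**The plan's own figures.** The death count is said to follow from this source: "in 2013 the number of deaths from cardiovascular diseases ranged from 2226 to 3086 per 100,000 inhabitants over 65 years of age". Over three years, 1000 × 3 × 0.02226 = 66.8 and 1000 × 3 × 0.03086 = 92.6. Compounding, 1000 × (1 − (1 − rate)³), gives 65.3 to 89.8. Neither reaches 100, but the source covers cardiovascular deaths only and an all-cause count could be higher. I take 100 as the planning figure; the mismatch does not bear on this point. For heart failure, 100 × 3 × 0.163 = 48.9, and at constant annual risk 100 × (1 − 0.837³) = 41.4, against the plan's minimum of 45.

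**Formulas** (constant hazards, t = 3 years; h = event hazard, m = death hazard)
- 1 − KM = 1 − exp(−h·t)
- True cumulative incidence: CIF = h/(h + m) × [1 − exp(−(h + m)·t)]
- Heart failure: h = −ln(1 − 0.163) = 0.178 per year, so 1 − KM = 1 − exp(−0.534) = 41.4%.
- Non-frail m solves 0.8 × [1 − exp(−3m)] + 0.2 × [1 − exp(−3·HR·m)] = 0.10.

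**Heart failure, equal hazard in both groups.** The death hazard ratio (HR) is an assumption; the article gives none.

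| Death HR | 3-year mortality, non-frail / frail | CIF, non-frail | Overstated by | CIF, frail | Overstated by |
|---|---|---|---|---|---|
| 2 | 8.5% / 16.2% | 39.7% | 1.6 points | 38.2% | 3.2 points |
| 3 | 7.4% / 20.5% | 40.0% | 1.4 points | 37.3% | 4.0 points |
| 4 | 6.6% / 23.8% | 40.1% | 1.3 points | 36.7% | 4.7 points |

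Example, HR 3, frail: m = 0.0766; CIF = 0.1779/0.2545 × [1 − exp(−0.7635)] = 0.699 × 0.534 = 37.3%.

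**Variations**
- Heart failure hazard doubled in frail patients: the overstatement there is 4.5 to 6.8 points. At death HR 3, the frail minus non-frail risk difference is 24.3 points by 1 − KM and 19.9 by CIF.
- An event at an assumed 5% per year: about 0.5 points in non-frail patients. In frail patients it is 1.2 to 1.7 points with equal event hazards and 2.1 to 3.1 if theirs is doubled.
- Cardiovascular death, assumed to be 50–70% of deaths, death HR 2 to 3: at most 0.1 points non-frail and 0.3 to 0.6 frail.
- Total 3-year mortality of 20% instead of 10%, equal heart failure hazards, death HR 2 to 4: 6.3 to 9.4 points in frail patients.

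**Cox.** A simulation of 200,000 patients with death HR 3 and true heart failure hazard ratios of 1 and 2 gave 0.98 and 1.96 from Cox models with deaths censored. The subdistribution hazard ratios were 0.90 and 1.76. Cox therefore recovers the cause-specific ratio.

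**The case against.** Four points can be made against the concern.

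First, the stated purpose is to find associated variables, and section 2.8 speaks of modelling hazard ratios. A Cox model that censors deaths does this properly. This stands: a reader might infer that the planned Cox models are biased by competing deaths, but as cause-specific models they are not. They simply do not give absolute risk on their own.

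Second, the Kaplan–Meier wording refers to survival and could mean mortality curves only. The article never says that it will report 1 − KM as the risk of a non-fatal outcome, nor that deaths will be plain censoring. This stands in part. A reader might infer a commitment to biased risk estimates, and the text does not go that far. But the same sentence extends the methods to the occurrence of outcomes generally, no other curve or risk estimator is named, and the declared uses are risk groups and individual risk.

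Third, an article condenses a fuller plan, so silence on competing events is not a fault. Agreed. The point rests on the estimator that is named, which does not suit some of the outcomes listed.

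Fourth, the size is easily exaggerated. The 16.3% rate belongs to about 100 STEMI patients; at 20% frail that is some 20 people, in whom a 40% risk has a standard error of √(0.4 × 0.6/20), about 11 points, well above the bias. A wide mortality contrast such as 25% against 6% implies a death hazard ratio of ln(0.75)/ln(0.94) = 4.65, which the article does not support. Both remarks are fair, and the range in the working is accordingly 2 to 4. Sampling error does not excuse a bias that leans one way and follows the exposure, but it does limit how much weight the point can bear.

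**Conclusion.** The concern holds for absolute risk of the non-fatal outcomes. Kaplan–Meier with deaths censored would overstate three-year heart failure risk by about 3.2 to 4.7 points in frail patients and 1.3 to 1.6 in non-frail patients. That is a difference of roughly 1.5 to 3.5 points between groups that owes nothing to heart failure itself. For events near 5% per year the overstatement in frail patients is about 1 to 3 points. For cardiovascular death it is about 0.3 to 0.6 points and of little practical weight.

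These figures assume constant hazards, the plan's mortality and frail share, extension of a one-year STEMI rate to three years, and a death hazard ratio of 2 to 4. They grow if mortality exceeds the planned 10%.

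All-cause mortality, on which the power statement rests, and the composite containing death are not affected. This is an inexpensive improvement in estimation, not a flaw that undermines the study.

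**What to change.** In section 2.10:

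1. Keep Kaplan–Meier for all-cause death and for composites that include death.
2. For new-onset heart failure, readmission, re-infarction, re-intervention and stroke, present Aalen–Johansen cumulative incidence by frailty group with death as a competing event. For cardiovascular death do the same, with non-cardiovascular death as the competing event.
3. Keep the Cox models and label their results for these outcomes as cause-specific hazard ratios.
4. Take any predicted absolute risk or risk group for these outcomes from a model that accounts for competing death, either combined cause-specific hazards or Fine–Gray.

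The deaths and events needed are already among the outcomes followed, so no new data are required. The cost is a few sentences, slightly more analysis, and possibly other software if the named package lacks these methods (an assumption that I have not checked).

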**Figure 2 F2:**
[figure not shown]
A plot of study power versus type I error for the sample size of 1000 patients and 2 different 1-year mortality rates.

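### The cited cardiovascular mortality rates give about 67 to 93 deaths in 36 months, not the approximately 100 that section 2.10 derives from them

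*Protocol article*

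**What the plan says.** The cohort size is fixed in section 2.1 (Patient population): "One thousand patients aged ≥65 years with symptomatic coronary heart disease will be enrolled". Section 2.10 (Statistical analysis) gives national statistics as its source: "in 2013 the number of deaths from cardiovascular diseases ranged from 2226 to 3086 per 100,000 inhabitants over 65 years of age". The next sentence draws the event count from that source alone: "These data allow to predict the occurrence of approximately 100 deaths in the study population during 36 months of prospective observation".

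Two things then rest on the mortality figures. Power: "Power of study based on the mortality data is presented in Fig. 2". Modelling: section 2.10 says that its event assumptions (this count and a separate one for heart failure) were needed for reliable Cox models, at ten complete observations for each variable estimated.

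The endpoint is in section 2.7 (Study outcomes): "we will monitor 3-year mortality, either all-cause and cardiovascular, re-infarction, re-intervention, stroke, new-onset heart failure, any hospital readmission". So mortality is counted over three years, both from any cause and from cardiovascular causes.

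**The concern.** A range of annual rates is cited, and one event count is said to follow from it. That count lies above everything the range can produce. The text states no adjustment for coronary disease, for non-cardiovascular death or for ageing during follow-up that would bridge the gap.

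The source and the endpoint also differ in two ways. The source covers cardiovascular deaths only, in all inhabitants over 65. The study counts deaths from any cause as well, in patients with symptomatic coronary disease.

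At stake is the number of variables the mortality model can carry under the article's own rule. The candidates are many: the Fried and IADL scales, several risk scores, arterial stiffness, body composition, lung function and biomarkers, with selection at a significance level below 0.1. An event count without a sound derivation gives no firm limit on that model and no firm input for power.

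**Working it through.** **Inputs**
- N = 1000 (section 2.1).
- Annual rate r = 2226/100,000 = 2.226% to 3086/100,000 = 3.086% (section 2.10; a one-year figure for 2013).
- Follow-up of 3 years (sections 2.7 and 2.10).
- Stated result: approximately 100 deaths (section 2.10).
- No loss to follow-up is applied; any loss would lower every count below.

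**Attempt to reproduce 100**

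| Method | r = 2.226% | midpoint 2.656% | r = 3.086% |
|---|---|---|---|
| Linear, N × 3r | 66.8 | 79.7 | 92.6 |
| Compounded, N × (1 − (1 − r)³) | 65.3 | 77.6 | 89.8 |
| Exponential, N × (1 − exp(−3r)) | 64.6 | 76.6 | 88.4 |

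For example, 1000 × 3 × 0.03086 = 92.6, and 1000 × (1 − 0.96914³) = 89.8. No cell reaches 100.

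**Rate that 100 deaths would need**
- Linear: 100/(1000 × 3) = 3.33% a year.
- Compounded: 1 − 0.9^(1/3) = 3.45% a year.

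Both exceed the cited maximum of 3.086%.

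**Size of the gap**
- Linear: 100/92.6 = 1.08 and 100/66.8 = 1.50, so 100 is 8% to 50% above the derived count.
- Compounded: 100/89.8 = 1.11 and 100/65.3 = 1.53, so 11% to 53% above.

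**Variables at ten per variable** (reading a complete observation as an event)
- 100 deaths: 100/10 = 10.
- Cited rates, linear: 66.8/10 = 6.7 to 92.6/10 = 9.3, so about 6 to 9.

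**Illustration of the effect on power.** The assumptions here are not the plan's design values. They are 20% frail, borrowed from the cited percutaneous-intervention study, for which the Introduction says that its authors "reported that approximately 20% of those patients is frail"; a two-sided 5% level; and chosen hazard ratios. By Schoenfeld's formula, the hazard ratio detectable with 80% power is exp((1.96 + 0.842)/√(D × 0.2 × 0.8)) for D deaths.

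| Deaths D | Detectable hazard ratio | Power at hazard ratio 2.0 |
|---|---|---|
| 100 | 2.01 | 79% |
| 93 | 2.07 | 76% |
| 67 | 2.35 | 62% |

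The effect is small at the top of the cited range and material at the bottom.

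**The case against.** The strongest reply is that 100 may be a reasonable forecast. Symptomatic coronary patients would be expected to die at least as often as the general population over 65, and counting non-cardiovascular deaths can only add to the total. All-cause deaths could then equal or exceed 100. This stands as a statement about the true count. It does not rescue the derivation, because section 2.10 attributes 100 to the cited data and states no uplift. It does rule out the inference that the event count is too favourable or the study underpowered: the documents give no rate that would settle the direction.

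A second reply is that 93 is close enough to be called approximately 100. That holds only for the highest rate, counted linearly, with no loss to follow-up. The midpoint gives 77 to 80.

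Two other readings are tempting and are not supported.
- The caption of Fig. 2 reads: "A plot of study power versus type I error for the sample size of 1000 patients and 2 different 1-year mortality rates". A reader might infer that the power calculation ignores frailty or the three-year horizon. The figure is not available here. The two rates could be those of frail and non-frail patients, the ends of the cited range, or annual inputs to a 36-month calculation.
- A reader might infer that the 100 deaths justify enrolling 1000 patients. The article fixes 1000, shows power for that number and ties the event counts to Cox modelling. It does not derive the sample size from the deaths.

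**Conclusion.** The point holds as an error of derivation in a figure that the plan relies on. Using the article's own inputs, the cited rates predict 67 to 93 cardiovascular deaths (65 to 90 compounded), and no rate in the cited range gives 100. The rates also describe a different population and a narrower cause of death than the endpoint, so they cannot establish an all-cause count in either direction.

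The arithmetic assumes complete follow-up and a constant annual rate. The range of 6 to 9 variables applies only if the cited rates are kept; it is not a fixed cap. The hazard ratios and power values above are illustrations and say nothing about the content of Fig. 2.

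**What to change.** In section 2.10, do one of the following:
1. Restate the expected count as about 67 to 93 cardiovascular deaths over 36 months (65 to 90 if compounded), naming the method.
2. Derive an all-cause count from a stated annual mortality rate in a comparable coronary cohort, showing the rate and the calculation. This matches the endpoint better.

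Then set the number of variables in the mortality model from that count by the article's own rule of ten per variable (about 6 to 9 under option 1), and make sure that the stated power uses the same 36-month count.

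The cost is a few sentences, plus a recalculation of power if it used a different count. The stated figures may become less favourable. No extra patients are needed, and no endpoint or procedure changes.
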